### 2.7. Interventions

#### 2.7.1. ILIB protocol.

The laser treatment will be performed by a speech therapist, using the wavelength of 660 nm. It will be done once a week for 4 weeks, in 20-minute sessions. In the CG, the ILIB procedure will be simulated, but with the laser turned off.

#### 2.7.2. Orofacial MFT.

MFT will be performed by a speech therapist specialized in the area. It will consist of 1 weekly session, where the functions of breathing, chewing and swallowing will be evaluated and addressed.

The following exercises will be indicated: nasal hygiene, inflated cheeks with the tip of the tongue on the palate, lingual sweep, tongue thrust against the palate, tongue touch on the last molars, chewing of soft solids and bolus assembly (20 minutes therapy session).

## 3. Outcome measures

All participants will undergo a parent or referent bruxism questionnaire, infant sleep quality questionnaire, nocturnal oximetry, and clinical assessment of orofacial functions at baseline and after 4 weeks of treatment. Patient retention and complete follow-ups are expected due to the treatment of bruxism symptoms.

### 3.1. Oximetry

Recorded sleep oximetry monitoring has high specificity and sensitivity for the diagnosis of respiratory disorders in children. This is the primary outcome of the study.

A portable pulse oximeter that includes Masimo SET® Measure-through Motion and Low Perfusion™ pulse oximetry under motion and low perfusion conditions. Nocturnal oximetry will be performed prior to treatment and post treatment. The parents or guardian of the minor will be trained.

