## Abstract

**Methods::**

This study will be a randomized controlled clinical trial. A triage of individuals between 4 and 17 years old with a diagnosis of sleep bruxism will be carried out at the clinic of the Catholic University of Uruguay, and in a private office referred by different private care centers. The selected participants will be evaluated before and after treatment by means of questionnaires on bruxism, sleep quality and nocturnal oxygen saturation measurement. For this, 46 patients with sleep bruxism will be recruited, who will be divided into 2 groups: control group (CG), which will undergo an application of placebo ILIB and an orofacial myofunctional therapy (MFT) exercise protocol; and na ILIB group, which will carry out an active application of ILIB and an exercise protocol, this being once a week for 8 weeks. The laser treatment (808 nm) will be performed twice a week for 8 weeks. The values will be tested for normality by the Kolmogorov–Smirnov test. For the comparison between the groups, *t* test will be carried out, considering a level of significance of 0.5% (*P* < .05).

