### 2.4. Sample calculation

The sample was calculated to detect a significant difference between PBM and MFT with 80% power and a significance level of 5%, considering the oxygen saturation index. Based on the study by Aarab et al^[19]^ to detect a difference in saturation index, with an effect size of 0.53, the minimum number per group should be 23 participants per group (Fig. 2).

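### The primary outcome is a technique (overnight oximetry) with no variable named, and the undefined saturation index behind the sample size is not carried into the outcome or analysis sections

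*Protocol article*

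**What the plan says.** The protocol article refers to the oximetry measure in five places.

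- **Section 3.1 (Oximetry)** designates the primary outcome: "Recorded sleep oximetry monitoring has high specificity and sensitivity for the diagnosis of respiratory disorders in children. This is the primary outcome of the study". The rest of the section gives the device, the training of parents and the timing: "Nocturnal oximetry will be performed prior to treatment and post treatment".
- **Section 2.4 (Sample calculation)** sizes the trial "with 80% power and a significance level of 5%, considering the oxygen saturation index", and concludes that "with an effect size of 0.53, the minimum number per group should be 23 participants per group".
- **The abstract (Methods)** lists the assessments as "questionnaires on bruxism, sleep quality and nocturnal oxygen saturation measurement".
- **The objectives**, at the end of the Introduction, include the prevalence of nocturnal hypoxemia. No cut-off is given.
- **Section 3.8 (Statistical analysis)** says that the groups will be compared by a t test, without saying on which variable.

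**The concern.** A t test compares one number per participant. An overnight recording has to be reduced to that number, and there is more than one way to do it: an average level, a lowest level, a rate of events, or time spent below a cut-off. Section 3.1 does not choose among them, and does not say whether the number is the post-treatment value or the change from baseline. Section 2.4 uses a label that might settle the choice, but leaves it undefined and unconnected to sections 3.1 and 3.8.

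Two things are at stake. First, the effect size of 0.53 can describe only one parameter, so a reader cannot check that the sample size applies to the comparison that will be reported. Second, if the choice stays open until the data are in, whichever parameter separates the arms can be presented as the primary result at its full nominal significance.

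**Working it through.** **1. The plan's own figure.** The inputs, from Figure 2 in section 2.4, are one tail, dz = 0.5373031, alpha 0.05 and power 0.80. For a paired or one-sample t test with n = 23:

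- noncentrality = dz × √n = 0.5373031 × √23 = 2.5768
- critical t (22 df, one-sided 5%) = 1.7171
- power = 0.8027

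These match the figure, and n = 22 gives 0.786, so 23 is the smallest n that reaches 80%. The calculation reproduces, but it does not identify the variable. It contains only a standardised effect. No mean, standard deviation, unit or event definition is given from which the parameter could be recognised. (Whether a paired calculation suits a two-group comparison is a separate question and is not argued here.)

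**2. The sections side by side.**

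| Place | Oximetry quantity | Defined? | Linked to the primary test? |
|---|---|---|---|
| Abstract | nocturnal oxygen saturation | no | no |
| Objectives | prevalence of nocturnal hypoxemia | no cut-off | no |
| 2.4 | oxygen saturation index | no | by inference only |
| 3.1 | the recording itself | no variable | declared primary |
| 3.8 | none named | – | t test, variable not stated |

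No two of these rows use the same term, and no sentence ties the term in 2.4 to 3.1 or 3.8.

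**3. What an open choice could cost (illustration).** Suppose k parameters are each tested two-sided at 5%, there is no true effect, and the result is called positive if any one test gives P < .05. The article gives neither k nor the correlation between parameters, so both are assumptions. For independent parameters the chance is 1 − 0.95^k:

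- k = 2: 1 − 0.9025 = 9.8%
- k = 3: 1 − 0.8574 = 14.3%
- k = 4: 1 − 0.8145 = 18.5%

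For correlated parameters, 20,000 two-arm trials with 23 per arm were simulated, using equally correlated normal parameters and t tests on 44 df:

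| k | correlation 0.3 | 0.5 | 0.7 | 0.8 |
|---|---|---|---|---|
| 2 | 9.2% | 9.0% | 8.5% | 8.2% |
| 3 | 14.0% | 12.8% | 10.7% | 10.0% |
| 4 | 17.5% | 15.8% | 13.3% | 11.9% |

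A separate run of the same size gave 14.0%, 12.7% and 10.9% for k = 3, and 17.0%, 15.5% and 13.6% for k = 4, at correlations 0.3, 0.5 and 0.7. The runs agree within simulation error; the standard error near 17% is √(0.17 × 0.83 / 20,000) ≈ 0.3 percentage points. The range is therefore about 8% (two parameters, correlation 0.8) to about 17% (four parameters, correlation 0.3), against 5% for one variable fixed in advance. At correlation 0.9 the rates are lower: 7.1%, 8.1% and 9.4% for k = 2, 3 and 4.

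**The case against.** The strongest reply is that the sections are compatible. A saturation index is something an oximeter provides, a trial is normally sized on its primary outcome, and the natural reading is that section 2.4 names the variable to be taken from the recording in section 3.1. This stands in part. A reader might infer that the trial was powered on one variable and will be tested on another, but the article does not show that. It shows an undefined term and a missing link. The link also cannot be assumed, because nothing in 3.1 or 3.8 adopts the term.

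A second reply is that a journal article condenses a full protocol, which may settle event thresholds and artefact handling. That is fair for those details. The choice of the primary variable is different: the article has a section that declares the primary outcome and a section that powers it, and what they state does not connect.

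A third reply is that the competing parameters and the error rates come from outside the document. This also stands. Only nocturnal hypoxemia appears in the text as a further oximetry quantity. The rates depend on an assumed number of parameters, an assumed correlation and selective reporting. They are not the error rate of the planned test.

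Two further inferences should be resisted. The saturation index might be read as a desaturation index with a particular threshold, but no threshold appears in the article. Mean saturation might be said to have no room to improve in these children, but no baseline values are given, and the eligibility criteria in section 2.2 do not mention oxygenation.

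**Conclusion.** The point holds in this form: the primary outcome is a technique, the only candidate variable is an undefined label in the sample-size section, and the analysis section names no variable. The powered variable is not shown to be the tested one, and the primary parameter remains open to choice after the data are seen.

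The size is conditional. If the best of 2 to 4 parameters were reported, the false-positive rate would be about 8-17% in place of 5%. This assumes correlations of 0.8 to 0.3, two-sided 5% tests, 23 per arm and no true effect. With one variable fixed in advance it stays at 5%. No revised sample size can be derived, because the article gives no mean, standard deviation or effect for any named parameter. A full protocol or analysis plan that is not shown may already fix the variable; in that case the article needs only to state it.

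**What to change.** 1. In section 3.1, name and define one primary oximetry variable: whichever one the saturation index in section 2.4 refers to. If it is an event index, give the event definition or cut-off.
2. Use the same name and definition in sections 2.4, 3.1 and 3.8.
3. In section 3.8, compare the arms on the post-treatment value of that variable, adjusted for the baseline recording that is already planned. This replaces the plain t test for the primary outcome with an analysis of covariance and settles the choice between post-treatment value and change.
4. Label all other oximetry quantities, including nocturnal hypoxemia, as secondary.
5. State the time of the post-treatment recording once the passages on treatment length are reconciled: sections 2.3, 2.7.1 and 3 say 4 weeks, and the abstract says 8 weeks.

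The cost is a paragraph of wording and one changed analysis line, with no extra recordings or visits. The downside for the sponsor is that it can no longer fall back on another oximetry parameter if the named one shows no difference.

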Regarding therapeutics, they are mostly palliative, addressing the symptom, but without providing a solution. A systematic review suggests that the evidence is still scarce in relation to drugs.^[11]^ Botulinum toxin protects orofacial structures (teeth, jaw muscles, temporomandibular joint) reducing the damage caused by bruxism, generating a decrease in pain and symptoms related to excessive muscle contraction.^[12]^ Occlusal devices, such as splints, are used to protect teeth from the damage caused by clenching and grinding during bruxism.^[13]^ Photobiomodulation (PBM) is a very promising, painless and low-cost option; capable of stimulating or inhibiting cellular processes.^[14]^ Intravascular Irradiation of Blood (ILIB), a systemic modality of PBM, can be used as a complementary therapy to other therapies.^[15]^ It emits energy that activates neurohumoral regulation and synchronization and cell modulation with antioxidant, metabolic, immunological, antispasmodic, sedative, healing, analgesic, anti-inflammatory and blood circulation-increasing effects.^[16,17]^ Orofacial myofunctional therapy (MFT) is a set of techniques and procedures whose objective is to promote changes in muscle patterns and orofacial functions through isotonic and isometric exercises with the orofacial and oropharyngeal muscles supported by the functions of breathing, chewing, swallowing and talk.^[18]^ Orofacial MFT and systemic low intensity laser administration are options to more traditional therapies.

The objective of this study is to determine the efficacy of ILIB in sleep bruxism, in combination with oral MFT. It also aims to evaluate the relationship between oxygenation and bruxism during sleep and to determine the prevalence of nocturnal hypoxemia and its association with daytime oral breathing.

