### 3.6. Presence of bruxism

The bruxism questionnaire will be delivered to parents or guardians, which will be completed prior to treatment and afterwards. The questionnaire contains 4 questions regarding the perceived presence of bruxism, and 5 questions for the dentist to answer, based on a clinical observation. All questions have the options “yes” or “no.” The more times the word “yes” is chosen, the greater the risk for bruxism is.

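### The primary outcome, nocturnal oximetry, does not measure the main objective, efficacy in sleep bruxism, so the primary result alone can neither show nor refute that efficacy

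*Protocol article*

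**What the plan says.** The Introduction of the protocol article closes with the aims. The first reads: "The objective of this study is to determine the efficacy of ILIB in sleep bruxism, in combination with oral MFT". A second sentence adds further aims: "It also aims to evaluate the relationship between oxygenation and bruxism during sleep and to determine the prevalence of nocturnal hypoxemia", together with the association of hypoxemia with daytime oral breathing.

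Section 3.1 (Oximetry) names the primary outcome and gives its reason: "Recorded sleep oximetry monitoring has high specificity and sensitivity for the diagnosis of respiratory disorders in children. This is the primary outcome of the study". Section 2.4 (Sample calculation) sizes the trial at 23 per group, "considering the oxygen saturation index".

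Bruxism is assessed before and after treatment under Section 3.6: "The questionnaire contains 4 questions regarding the perceived presence of bruxism, and 5 questions for the dentist to answer". All items are yes/no, and more positive answers mean a greater risk of bruxism. This outcome is not primary and has no sample-size calculation.

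Section 2.2 requires a diagnosis of sleep bruxism at entry. None of its criteria concerns oxygen saturation or a respiratory disorder.

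**The concern.** The objective, the primary outcome and the sizing variable should all refer to the same thing. Here the objective is about bruxism, while the other two are about oxygenation. If the primary comparison is significant, the natural sentence in the report is that ILIB is effective in sleep bruxism, and the test would not support it. If the comparison is not significant, the natural sentence is that ILIB does not work in sleep bruxism, and that would be equally unsupported. What is at stake is the trial's main conclusion in either direction.

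**Working it through.** The question turns on whether the protocol's parts fit together, so most of the check is a comparison of sections. One figure can be reproduced, and it shows what the trial was sized for.

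**1. The stated calculation.** Inputs from Figure 2: one tail, dz = 0.5373031, alpha = 0.05, n = 23.

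- Noncentrality: dz × √n = 0.5373031 × √23 = 2.5768 (stated 2.576815).
- Critical t, one-sided 5%, 22 degrees of freedom: 1.7171 (stated 1.7171444).
- Power from the noncentral t: 0.8027 (stated 0.8027361). With n = 22 it is 0.786, so 23 is the smallest n that reaches 80%.

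The output reproduces. By Section 2.4 its variable is oxygen saturation. The protocol gives no effect size, standard deviation or response rate for the bruxism questionnaire, so no corresponding figure for bruxism can be computed. (The calculation is of the paired or one-sample, one-sided type, while Section 3.8 plans a between-group t test. That is a separate matter and plays no part here.)

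**2. Could a test on saturation support a claim about bruxism?** There are three possible routes.

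- *Saturation is itself a measure of bruxism.* The protocol does not say so. Its only stated reason for the choice concerns respiratory disorders: "Recorded sleep oximetry monitoring has high specificity and sensitivity for the diagnosis of respiratory disorders in children".
- *Saturation is an established surrogate for bruxism.* The protocol does not claim this either. The Introduction makes the relationship an aim still to be evaluated. Even if an association were found in this trial, a correlation between children would not show that a treatment effect on saturation carries over to bruxism.
- *The objective is itself about saturation.* The first-stated objective is not. The further aims do involve oxygenation, but they concern association and prevalence, not the effect of ILIB.

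**3. What each primary result would permit, as the plan stands.**

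| Primary result | On nocturnal oxygenation | On efficacy in bruxism |
|---|---|---|
| Groups differ | Evidence of an effect of ILIB added to MFT | None directly; bruxism may or may not have changed |
| No significant difference | No effect demonstrated | None directly; bruxism may still have improved |

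The right-hand column is uninformative in both rows. Both groups receive MFT (Section 2.3), so the contrast isolates ILIB added to MFT. The gap therefore lies in the outcome and not in the comparison.

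**The case against.** Several points can fairly be made for the plan.

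- **Oximetry is not irrelevant.** The Introduction lists respiratory problems among the factors related to bruxism, and Section 2.7.2 says that MFT addresses breathing. This stands as a rationale for measuring saturation. It does not make saturation a measure of bruxism, since respiratory problems are one item in a long list of possible factors.
- **The trial has more than one aim.** Oximetry serves the aims on oxygenation and hypoxemia. This stands, and it limits the point to the main efficacy objective.
- **Bruxism is still measured in both groups.** This stands too. The trial can report on bruxism, but from a non-primary outcome with no sample size. Bite force (Section 3.4) may also bear on it: the Discussion cites reduced bite force as part of a response in children with sleep bruxism. It would thus go too far to call the questionnaire the only bruxism-related measure, although it is the only one the protocol presents as assessing the presence of bruxism.
- **Oximetry is objective and the questionnaire is not.** Part of the questionnaire is parent perception and part is a dentist's observation. Section 2.6 describes blinding of participants only. The Introduction says that only polysomnography is considered definitive. This is a good reason not to insist on making the questionnaire primary.

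A reader might also infer three stronger things. The first is that most children will have normal saturation and no room to improve. The absence of a saturation criterion in Section 2.2 leaves that open but does not show it, and the protocol treats the prevalence of hypoxemia as unknown. The second is that the exact oximetry index is unspecified and could be chosen after the data are seen. An article may leave that detail to the full protocol or analysis plan, which are not shown. The third is that a loss of power or an inflated false-positive rate can be attributed to the choice of outcome. The documents give no basis for such a figure.

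**Conclusion.** The concern holds for the main objective. The primary outcome and the sizing variable are nocturnal oxygenation, the first-stated objective is efficacy in sleep bruxism, and the protocol itself leaves the link between the two open. The primary result alone can therefore neither establish nor refute efficacy in bruxism. No unseen analysis plan could repair this, because the objective, the primary outcome and the sizing variable are all stated and do not match.

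The size of the problem is not numerical: it is the whole inference from the primary test to the main objective. The conclusion assumes that the first-stated objective is the main one and that the oximetry variable means oxygen saturation, as Section 2.4 indicates.

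A reader might go further and say that the trial cannot answer its question at all, or that oximetry must be replaced. The documents do not support either. Oximetry serves the further aims, bruxism is recorded in both groups, and the mismatch can be removed without changing the primary outcome.

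**What to change.** 1. Keep nocturnal oximetry as primary. Restate the primary objective and the permitted conclusion as the effect of ILIB added to MFT on nocturnal oxygenation in children with sleep bruxism.
2. State explicitly that no claim of efficacy in bruxism rests on the primary result, whichever way it falls.
3. Name the bruxism questionnaire score (the number of yes answers, 0 to 9, from 4 + 5 items) as key secondary outcome, reported as supportive and not powered.

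The cost is a wording amendment to the protocol, with the registry entry brought into line where needed. No new measurement is required. The amendment should be dated and made before results by group are seen. The real price is that the trial gives up a primary claim about bruxism, which its present design could not support.

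The sponsor may prefer to make the questionnaire score primary, which would match the stated objective directly. That would require a new sample-size justification, for which the protocol supplies no inputs, so 46 children may or may not suffice. It would also require that the dentist's items be scored blind to group.

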### 3.2. Breathing

A clinical evaluation will be carried out by a speech therapist specialized in the area of Orofacial Motricity, to check for possible improvement in breathing. It is the respiratory characterization from the taking of air, which explains the anatomical and topographical situation of its entrance to the respiratory system (respiratory mode), to the thoracoabdominal movement zone that integrates inspiration and expiration. It is supported by the observation with the aid of a Glatzel’s mirror to anatomically determine the upper airway status and its functional correlation.

### 3.3. Swallowing

A clinical evaluation will be carried out by a speech therapist specialized in the area of Orofacial Motricity, to check for possible improvement in swallowing. For this, the Payne’s test, which assesses tongue posture both at rest and in function (swallowing), will be used. From instruments such as liquid fluorescein applied to the apex lingual and lateral borders, and Payne’s lamp that verifies the vestige of the fluorescein, and therefore the conditions of support, thrust, position and/or obstruction of the tongue.

### 3.4. Chewing

A clinical evaluation will be carried out by a speech therapist specialized in the area of Orofacial Motricity, to check for possible improvement in chewing. For this, the gnathodynamometer, test that allows to measure the force of the occlusion, will be used.

